### Recruitment, enrollment, and randomization

Potential participants will be identified via patient partner organizations (e.g., the Portuguese Society of Clinical Sexology), university mailing lists, faculty newsletters, patient conferences, and social media platforms. Clinical centers will be notified about the study and supplied with promotional materials that guide interested people to the recruiting website/link for further information and registration. Participants will be invited to participate by filling in an expression of interest survey. A consent form will be executed during registration, followed by the eligibility criteria (T0) screening administered via a telephone interview (LimeSurvey GmbH, n.d.). After completing the online baseline assessment (T1), participants fulfilling all eligibility criteria will receive an informative audiovisual material through email. Such a video will contain a step-by-step guide on how participants will access, use, and complete the program. Maximal procedure randomization will be implemented by a team member using computerized software to create allocation tables (Clinical Trial Randomization Tool, n.d). Participants will be randomly allocated 1:1 to the two study arms (Figure 1). Randomization will also allocate a nested sample (n = 20) to an embedded assessment moment (T1 and T2). This sample will undergo complementary laboratory-based assessments intended to explore potential intervention-related changes in neural activity associated with cognitive and behavioral aspects of sexual response and sexuality in general. Measurements will encompass EEG functional connectivity and exploration of ERPs of sexual implicit cognitions (through an Implicit Association Task). Laboratory tasks will also include a physiological (thermography) plus self-reported body-heat sensations (genital temperature) assessments, intending to explore the relation between both variables as representative of sexual interception abilities.

**Figure 1. F0001:**
[figure not shown]
FULLSENSE pilot feasibility randomized controlled trial participant flow diagram. *Note*. PRO = participant-reported outcome.

Based on attrition rates observed in similar 8-week online trials, we anticipate a retention rate of approximately 70–75% (i.e., a predicted attrition of 25–30%) (Zarski et al., 2022). To maximize participant engagement throughout the 8-week period, several retention strategies will be implemented. Specifically, participants will receive regular check-ins and support via email communication with the research team to address any technical or logistical issues and to promote adherence. In addition, weekly automated reminders will be sent to prompt module completion.

### Intervention delivery and assessment

FULLSENSE (Figure 2) is an 8-week, digitally delivered online program designed to promote sexual health and well-being in adults experiencing sexual dysfunction through a cognitive-behavioral approach. Participatory design (Bødker & Kyng, 2018) involving secondary end-users (psychologists and sexologists) and agile framework (Hekler et al., 2016), were implemented for program development. The program adopts a transdiagnostic structure featuring sexual health intervention strategies considered appropriate for the different populations under study according to efficacy studies and reviews of literature (Avery-Clark, Weiner, & Adams-Clark, 2019; Berner & Günzler, 2012; Doğan, 2023; Fahami, Pahlavanzadeh, & Asadi, 2015; Günzler & Berner, 2012; Krieger et al., 2023; Mahar et al., 2022; Sharifipour et al., 2024; Zarski et al., 2022). Core components include psychoeducation (Zippan, Stephenson, & Brotto, 2020), cognitive restructuring (Beck, 2020), mindfulness (Brotto, 2013; Brotto, Stephenson, & Zippan, 2022), masturbation training (Both & Laan, 2008; Semans, 1956), communication skills training (Rosenberg, 2002), exercises to heighten sexual sensation awareness and expand erotic repertoire (Brotto, 2013; Brotto, Stephenson, & Zippan, 2022), and sensate focus exercises (Masters & Johnson, 1966). The program is structured into eight weekly modules (Table 1).

**Figure 2. F0002:**
[figure not shown]
FULLSENSE overview.

**Table 1. t0001:** Structure and content of FULLSENSE.

Module	Intervention components	Content
1-Welcome and introduction	Psychoeducation	Welcome and Introduction Basic concepts of sexuality The different sexual dysfunctions Factors that influence sexuality Self-compassion
2-Sexual thoughts and beliefs	Psychoeducation Cognitive restructuring	Cognitive restructuring Sexual scripts and beliefs Thoughts, emotions and behaviors
3-Mindfulness	Psychoeducation Mindfulness	Mindfulness exercises
4-Body sensations	Psychoeducation Mindfulness Sensate focus	Sensate focus/ Interoceptive awareness Spectator syndrome and its impact
5-The body and pleasure	Psychoeducation Sexual skills training Mindfulness	Masturbation training Vulva and Penis’s Anatomy
6-Sensual exploration	Psychoeducation Sexual skills training	Sensual exploration Fantasy and kink
7-Communication	Psychoeducation	Communication Self-determination, consent and assertiveness
8-Change and progress	Relapse prevention	Overview of FULLSENSE and progress evaluation Strategies to maintain progress and prevent setbacks

Regarding human support, FULLSENSE will be delivered using a guided service model, which includes synchronous or asynchronous contacts, support, and feedback from psychologists via email, telephone, and other communication channels. Participants will obtain access to the intervention following preliminary screening assessment and online baseline assessments. The screening assessment (T0) aims to evaluate the fulfillment of the predefined eligibility criteria. In addition to the assessment of age, internet access, and concurrent engagement in psychological therapy or clinical trial, psychopathological symptoms (Patient Health Questionnaire-9 (PHQ-9); Kroenke, Spitzer, & Williams, 2001); Generalized Anxiety Disorder-7 (GAD-7); Spitzer et al., 2006, 57) and sexual dysfunction (Sexual Health Assessment of Practices and Experiences (SHAPE); WHO, 2023) will be evaluated in this initial screening.

After completing the online baseline (T1) assessment, participants meeting eligibility criteria will be registered and randomized, following an appointment with the assigned research member (Psychologist) to provide program access, examine the program’s framework (Figure 2), present the baseline findings, and establish therapeutic goals. The primary outcomes of this pilot trial are acceptability, usability (System Usability Scale (SUS) (Bangor, Kortum, & Miller, 2008) and feasibility measures (i.e., recruitment, randomization, retention, and adherence rates). Acceptability will be assessed in postintervention semistructured interviews. Secondary outcomes will evaluate preliminary efficacy on sexual beliefs (Sexual Dysfunctional Beliefs Questionnaire (SDBQ); Nobre & Pinto‐Gouveia, 2003), sexual satisfaction (Global Measure of Sexual Satisfaction (GMSEX); Lawrance & Byers, 1995), function (Index of Erectile Function (IIEF); Rosen et al., 1997b); and Female Sexual Functioning Index (FSFI); Rosen et al., 1997a), pleasure (Sexual Pleasure Scale (SPS); Sanchez, Crocker, & Boike, 2005) and distress (Female Sexual Distress Scale-Revised (FSDS-R); Derogatis et al., 2002). Additionally, participants will complete a self-report questionnaire to provide their sociodemographic and sexuality-related behavioral data, including age, gender, relationship status, religion, education, sexual orientation, and frequency of sexual activities. Changes in potential transdiagnostic factors, namely interoceptive awareness (Multidimensional Assessment of Interoceptive Awareness (MAIA; Mehling et al., 2012), trauma screening questionnaire (Posttraumatic Stress Disorder Checklist for DSM-5 (PCL-5; Weathers et al., 2013), questions about negative sexual experiences, mindfulness (Cognitive and Affective Mindfulness Scale-Revised (CAMS-R); Feldman et al., 2007), quality of life (World Health Organization Quality of Life: Brief Version (WHOQOL-BREF); The Whoqol, 1998), psychopathology (BSI-18; Derogatis, 2001), and therapeutic outcomes (Outcome Questionnaire (OQ-45); Lambert et al., 2004), will be assessed. As mentioned before, a subsample of participants will be invited to on-site laboratory sessions (at T1 and T2). Using a multimodal approach that combines EEG, behavioral tasks, thermal imaging, and self-report measures on affect (Positive and Negative Affect Schedule (PANAS; Watson, Clark, & Tellegen, 1988) and automatic thoughts (Sexual Modes Questionnaire - Thoughts Subscale (QMS; Nobre & Pinto‐Gouveia, 2003), this complementary part of the study will allow us to explore how brain activity, implicit cognitions, and interoceptive awareness contribute to intervention-related changes in sexual functioning and perception.

Participants will be instructed to conclude each module within a week. Within 24 hours before the pre-defined timeframe for module completion, the assigned research member will evaluate participants’ progress based on the reported results and decide whether participants will have access to the subsequent module. Such results will be shared with the participants, and, if deemed required, further instructions will be provided on the steps to proceed to the forthcoming module. The intervention’s initial effectiveness will be evaluated upon program completion at posttest (T2 for arm 1 and T1rep for arm 2), utilizing the aforementioned measures, and a final interview for debriefing, user-experience and acceptability assessment.

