**Methods:**

A two-arm, parallel, open-label design, with the waiting-list control group receiving treatment as usual will be conducted. Participants (N = 70) meeting eligibility criteria will be randomly assigned to the FULLSENSE intervention or a waiting-list control group. Primary outcomes will assess the intervention’s acceptability, usability, and feasibility. Secondary outcomes will evaluate preliminary efficacy in improving sexual satisfaction, functioning, pleasure, and reducing sexual distress, while cognitive and neurophysiological assessments will allow us to explore functional connectivity and correlates of implicit cognition and interoception. Data collection will include self-reported measures and neurophysiology assessments for a nested sample.

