The total sample size of (35 per arm) is **not intended for statistical power to detect treatment efficacy**. Consistent with recommendations for pilot trials, this sample size is adequate to assess the primary outcomes of **feasibility, acceptability, and usability**, and to provide a robust **estimation of effect sizes and attrition rates** necessary for calculating the required sample size of a future, fully powered definitive trial The study employs a within-subject design with a high number of trials per participant and fine-grained EEG/ERPs measures, which substantially increases statistical power. This approach allows for the detection of subtle intervention-related effects at the individual level and minimizes inter-individual variability. From a statistical standpoint, the large number of repeated measures per participant provides a rich dataset for reliable estimation of within-person changes, even with a smaller N.

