As aforementioned, this feasibility pilot trial has several strengths, including its RCT design, the inclusion of diverse sexual dysfunctions (both male and female), the use of validated outcome measures, and its comprehensive and transdiagnostic nature. Nevertheless, some limitations must be acknowledged. While adequate for feasibility testing, the sample size may limit the generalizability of the findings and preclude definitive conclusions about efficacy. Initially designed for evaluative training courses, the platform may not be optimally suited for the program’s learning and reflection exercises, potentially impacting user experience, especially for smartphone users. Consequently, recruitment and retention of participants may present challenges, so future optimization of the platform for smartphone use might also be crucial. A key limitation of this protocol, inherent to its pilot nature, is the **small sample size (N = 70)**. While sufficient for assessing feasibility and generating preliminary effect sizes, the study is **not powered to draw definitive inferential conclusions** regarding the efficacy of the FULLSENSE intervention. The results must therefore be interpreted cautiously and strictly within the context of **viability and preparatory data** for a larger trial Also, the participatory design approach did not include its primary end users, which may influence acceptability and feasibility. We acknowledge the limitation that, due to its general design, the program may not fully reflect the specific, nuanced experiences of all sexual and gender minority groups, which may influence individual engagement. We clarify that future qualitative research will be essential to explore these differences in depth.

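### Acceptability, a primary outcome, rests on one interview tied to programme completion, so its findings will probably come mainly from those who stayed and are likely to be too favourable

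*Protocol article*

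**What the plan says.** The section Intervention delivery and assessment sets the outcome hierarchy: "The primary outcomes of this pilot trial are acceptability, usability (System Usability Scale (SUS"), followed by feasibility rates for recruitment, randomisation, retention and adherence. For acceptability it gives a single method: "Acceptability will be assessed in postintervention semistructured interviews". The last paragraph of that section gives the timing. The intervention's initial effectiveness "will be evaluated upon program completion at posttest (T2 for arm 1 and T1rep for arm 2"), and the same sentence adds "a final interview for debriefing, user-experience and acceptability assessment".

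The section Recruitment, enrollment, and randomization gives the expected loss: "we anticipate a retention rate of approximately 70–75% (i.e., a predicted attrition of 25–30"%). The Discussion says the platform was built for another purpose and may suit the exercises poorly, "potentially impacting user experience, especially for smartphone users". It then presents difficulty with recruitment and retention as a consequence.

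The article describes no interview, questionnaire or reason-for-stopping item for people who leave early. Data analysis says that the final-interview data will be analysed, and it limits intention-to-treat to comparisons between the arms.

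**The concern.** People who find the programme or the platform unacceptable are among those most likely to stop. If the only acceptability measure is taken when the programme ends, their views are the ones most likely to be missing. The article itself supports this link, since the Discussion treats poor user experience as a cause of retention problems.

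The aims are also wider than completers. Objectives and hypotheses predicts good acceptance by participants, and Study design says the pilot is meant to find shortcomings before larger trials. A favourable account from those who stayed would answer a narrower question. It could also carry an avoidable weakness of the programme into the later trials.

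**Working it through.** **Inputs from the article**
- Total sample: "Participants (N = 70) meeting eligibility criteria will be randomly assigned" (Abstract, Methods).
- Per arm: "The total sample size of (35 per arm) is" followed by the statement that it is not set for power (Participants and eligibility criteria). Allocation is 1:1.
- Retention 70–75%, attrition 25–30% (Recruitment, enrollment, and randomization).

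**Reproducing the stated figures**
- 2 × 35 = 70, as stated.
- 1 − 0.75 = 0.25 and 1 − 0.70 = 0.30, as stated.

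**How many views could be missing.** This assumes that the overall attrition rate applies equally to the intervention arm, which the article does not say.
- Leavers: 35 × 0.25 = 8.75 and 35 × 0.30 = 10.5, so about 9 to 11.
- Remaining: 35 × 0.75 = 26.25 and 35 × 0.70 = 24.5, so about 24 to 26.

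**Direction of the bias.** Suppose, for illustration only, that acceptability were summarised as the proportion who find the programme acceptable. Let d be the proportion leaving, pc the proportion accepting among completers and pd the proportion among leavers. The proportion among all is (1 − d)pc + d·pd. A figure from completers alone therefore differs from it by

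pc − [(1 − d)pc + d·pd] = d(pc − pd).

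The article gives neither pc nor pd. All values in the table are assumed.

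| pc | pd | All, d = 0.25 | All, d = 0.30 | Completers minus all (points) |
|---|---|---|---|---|
| 0.90 | 0.30 | 0.750 | 0.720 | 15 to 18 |
| 0.90 | 0 | 0.675 | 0.630 | 22.5 to 27 |
| 0.80 | 0.50 | 0.725 | 0.710 | 7.5 to 9 |
| 0.80 | 0.80 | 0.800 | 0.800 | 0 |
| 0.80 | 1.00 | 0.850 | 0.860 | −5 to −6 |

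The difference is positive whenever leavers accept the programme less often than completers. It vanishes if the two groups agree and reverses only if leavers are the more accepting. The first case is the one that the Discussion's own reasoning points to.

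**What the other provisions cover**
- Retention and adherence rates count the leavers but do not record their views.
- Email check-ins and weekly reminders are described as support, not as a measure of acceptability.
- Intention-to-treat covers between-arm comparisons, and acceptability of FULLSENSE is not one.

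**The case against.** A reader might infer that early leavers are barred from the interview. The article does not say so. The timing phrase also covers the waiting-list arm at T1rep, which its label suggests is a repeat of baseline. For that arm the phrase seems to mean a scheduled time point. On the same reading, an intervention participant who stopped at module 3 could still be invited at T2. A full protocol or interview guide might also provide for exit contacts, which an article need not list. This stands, and it is why the conclusion is put as probable.

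A reader might also infer that acceptability will be overstated by a calculable amount. It cannot be calculated. The data are qualitative, no percentage or threshold is planned, and the rates in the table are invented to show direction.

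Nor can it be said that the usability scale shares this timing. The article gives the SUS no time point, and the measures repeated at posttest are mentioned in connection with effectiveness.

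Finally, it would go too far to say that the pilot could not detect an unacceptable programme. Retention and adherence are primary outcomes themselves and would fall if people left for that reason, and the platform's limits are disclosed. What these rates cannot supply is the reason for leaving.

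What remains is not mere silence. The article states an instrument and a timing for a primary outcome, and together they favour those who stay.

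**Conclusion.** The point holds as a probable selection bias in a primary outcome. As written, the plan would draw its acceptability findings mainly from the 24 to 26 intervention participants expected to remain. It would probably miss the views of about 9 to 11 others, and their reasons for stopping.

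The findings are likely to be too favourable. This rests on three assumptions: that the predicted attrition applies equally to the intervention arm, that leavers are seldom reached by an interview tied to the end of the programme, and that they think less well of the programme than completers do. The article's own account of the platform supports the third but does not prove it. No numerical size can be attached.

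The change is worth making because the outcome is primary, the loss is foreseen and the remedy is small.

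**What to change.** State that everyone randomised to FULLSENSE, including those who stop early, is invited to the acceptability assessment at week 8, or at withdrawal if that comes first. For leavers it can be a short telephone or email interview that asks the reason for stopping. Add a few closed acceptability items and the SUS for all, and state the SUS time point.

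Report the number assessed out of all randomised to FULLSENSE, and show completers and leavers separately. Counting non-responders as not accepting should be at most a sensitivity bound, because it would otherwise relabel attrition, which is already covered by the retention outcome, as poor acceptability.

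The cost is about ten short contacts by existing staff, through the email and telephone channels that the guided delivery already uses, plus a few survey items. Some leavers will not reply, and the result may look less favourable.

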## Data analysis

Descriptive statistics will be provided for demographic characteristics and outcome variables, including means and standard deviations for continuous variables and proportions for categorical variables. Independent sample t-tests and chi-square analyses will be conducted to evaluate potential baseline differences between participants assigned to the experimental and control groups to determine preliminary efficacy. The qualitative data collected in the final interview will be included in the analysis. For the data collected during the lab experiment, we will opt for a multimodal analytical approach. Behavioral and physiological data regarding sexual cognitions and interoception will be collected to explore underlying psychological and neurological processes and potential changes resulting from the intervention. Hence, for the within-subject factors (such as multiple time points or conditions in the ERP or thermal response experiments), rmANOVAs or Linear Mixed Effects (LME) models will be used for detecting overall differences across these conditions. Regression analyses will help in predicting outcomes, and correlations can offer insights into the strength and direction of associations. GMLL will allow us to model the random effects of individuals, accounting for the correlation among repeated observations and providing subject-specific insights. Differences between the experimental and control groups regarding secondary outcomes will also be analyzed. We will comply with the intention-to-treat (ITT) principle for comparisons between treatment groups.

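### The efficacy post-test and final interview are tied to program completion, an event undefined for the waiting-list arm and for intervention participants who stop or are held back, so the ITT comparison could not be properly carried out as written

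*Protocol article*

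**What the plan says.** All references are to the protocol article.

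- **Post-test trigger** (Intervention delivery and assessment, last paragraph): "initial effectiveness will be evaluated upon program completion at posttest (T2 for arm 1 and T1rep for arm 2"). The same sentence attaches the closing interview on user experience and acceptability. The text gives no week for T2 or T1rep.
- **Pacing and gating** (same section): "The program is structured into eight weekly modules (Table 1"), and "Participants will be instructed to conclude each module within a week". Near each module deadline a research member reviews progress to "decide whether participants will have access to the subsequent module".
- **Control condition** (Abstract, Methods): a two-arm design "with the waiting-list control group receiving treatment as usual will be conducted".
- **Analysis principle** (Data analysis): "We will comply with the intention-to-treat (ITT) principle for comparisons between treatment groups".
- **Size and attrition**: "The total sample size of (35 per arm) is" said not to be chosen for power (Participants and eligibility criteria). Under Recruitment, enrollment, and randomization, "we anticipate a retention rate of approximately 70–75% (i.e., a predicted attrition of 25–30" per cent). The attrition is not split by arm.
- **Outcomes** (Intervention delivery and assessment): acceptability, usability and feasibility are primary, and feasibility lists retention and adherence as separate rates. The efficacy questionnaires are secondary.

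**The concern.** An intention-to-treat comparison needs outcomes sought from everyone randomised, at comparable times since randomisation. The stated trigger is an event after randomisation that only one arm can have.

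Three things follow if site staff apply the sentence as written:

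1. Follow-up time can differ between arms, because a participant who is held at a module finishes later than the nominal 8 weeks.
2. A participant who stops has no defined T2, so outcomes may be missing in arm 1 for reasons linked to how the program was going.
3. The acceptability interview has the same trigger, so people who gave up, who have most to say about acceptability, have no defined interview. This touches a primary outcome.

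The pilot's stated purpose is to supply effect sizes and attrition rates for sizing a definitive trial (Participants and eligibility criteria). Both depend on who is assessed at post-test and when. An analysis plan can deal with missing values, but it cannot recover a questionnaire that was never sent.

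**Working it through.** **The plan's own figures.** 2 × 35 = 70, as stated. 1 − 0.70 = 0.30 and 1 − 0.75 = 0.25, so the attrition range is the complement of the retention range. The article gives no alpha, power, effect size or SD, so there is no power calculation to reproduce.

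**When each type of participant is assessed, applying the trigger literally.**

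| Participant | Program completed? | Time of post-test |
|---|---|---|
| Arm 1, on schedule | Yes, after 8 modules at 1 per week | Week 8 of the program |
| Arm 1, held back (say 2 modules, 1 extra week each; assumed) | Yes, late | 8 + 2 × 1 = week 10 |
| Arm 1, stops | No | Not defined |
| Arm 2 | No program before T1rep | Not defined by the trigger; only a calendar date can set it |

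The ITT sentence covers all four rows. The trigger gives a date for the first two only, and those two dates differ.

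**How many participants could be affected.** Assume that the overall attrition applies to arm 1 and equals non-completion there; the article does not say so. Then 35 × 0.25 = 8.75 and 35 × 0.30 = 10.5, or about 9 to 10 people without a T2, leaving 26.25 to 24.5 of 35.

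**Illustration 1: dilution.** Assume also that completers gain 0.5 SD over controls, that non-completers gain nothing, and that completers do not otherwise differ from controls.
- ITT effect = share completing × completer effect: 0.70 × 0.5 = 0.35 SD; 0.75 × 0.5 = 0.375 SD.
- Excess of the completer estimate: 0.5 − 0.35 = 0.15 SD; 0.5 − 0.375 = 0.125 SD.

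**Illustration 2: selection.** Let r be the share completing and ρ the correlation between propensity to complete and outcome (unknown, so a range is shown). The bias in SD units is ρ × φ(z_r)/r. The factor φ(z_r)/r is 0.497 at r = 0.70 and 0.424 at r = 0.75.

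| ρ (assumed) | r = 0.70 | r = 0.75 |
|---|---|---|
| 0 | 0 | 0 |
| 0.1 | 0.05 | 0.04 |
| 0.3 | 0.15 | 0.13 |
| 0.5 | 0.25 | 0.21 |

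**Precision, for scale.** The 95% half-width of a standardised difference is 1.96 × √(1/n₁ + 1/n₂).
- 35 v 35: 0.47 SD.
- 26.25 v 26.25 and 24.5 v 24.5 (stated retention in both arms): 0.54 and 0.56 SD.
- 26.25 v 35 and 24.5 v 35 (loss in arm 1 only): 0.51 and 0.52 SD.

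These figures show what could be at stake. They do not show that the trial plans such a comparison.

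**The case against.** The best reply is that the phrase is loose shorthand for the end of the 8-week period. The sentence applies it to both arms, and since arm 2 has had no program by then, it makes sense for both only as a study time point. Eight modules at one per week, each with a set deadline, support that reading. Figure 1, the participant flow diagram, is not available here and may give the timing. A condensed article may also leave visit windows and the follow-up of people who stop to a fuller document. Efficacy is secondary, and the article asks for caution in interpreting it.

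Much of this stands. A reader might infer that the planned comparison is completers against all controls, in contradiction of ITT. The article does not support that: nothing limits T2 or the analysis to completers, nothing says that all controls will be assessed, and ITT is stated outright. A reader might also infer that retention and adherence have become the same event in arm 1. That holds only if non-completers really are not assessed, and the article lists the two rates separately. Nor can the illustration be turned into a finding that effects will be overstated by some percentage or that the next trial will be too small. Its inputs are assumed, and its 0.125–0.15 SD shift is small beside a half-width of 0.54–0.56 SD.

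What does not stand is that the matter is only missing detail. The article states a trigger, and it is a poor one. The weekly schedule is an instruction to participants, and the gating step in the same paragraph allows departures from it, so the schedule does not fix the visit date.

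**Conclusion.** The point holds as a defect in a stated rule. Program completion does not exist as an event for the waiting-list arm before T1rep, and it is undefined for intervention participants who stop or are held back. Followed literally, the rule makes arm 1 assessment depend on adherence, and the ITT comparison could not be properly carried out. It is not a direct contradiction of ITT: a loosely anchored visit is compatible with analysing people as randomised, provided that they are assessed.

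The size of any bias is unknown. The figure of 0.5 SD against 0.35–0.375 SD rests on four assumptions: overall attrition equals arm 1 non-completion, none of those people has a T2, completers gain 0.5 SD, and non-completers gain nothing. Under the separate selection model the bias runs from 0 to 0.25 SD as the assumed correlation runs from 0 to 0.5. If the team already means the end of a common 8-week period for everyone, only the wording needs to change.

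**What to change.** Replace the completion trigger with a time anchor:

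1. Set T2 and T1rep at the same fixed time from randomisation in both arms (for example 8 weeks, with one stated window), for everyone randomised and regardless of modules completed. If program access starts some days after randomisation, choose the common time with that gap in mind.
2. Send the post-test questionnaires and the interview invitation also to intervention participants who stop the program.
3. Count retention as post-test data obtained, by arm, and adherence as modules completed, and report them separately.

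The cost is wording and some extra reminders, to about 10 people if the stated attrition applies in arm 1. The sample size, the modules and the gating need not change. The downside is that some intervention participants will be measured before they finish module 8, so the estimate describes being offered the program for that period rather than finishing it. That is the quantity an ITT comparison addresses. For participants already assessed under the present wording, time from randomisation to post-test should be reported by arm.
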